#### 2.5.2. Study Procedure

The study is schematically depicted in Figure 2. Data will be collected from participants before and after the intervention, using a specific questionnaire designed in order to evaluate the program (Appendix A Table A1). Due to the young age of the children, some limitations when reading and answering a questionnaire are expected, and so they will complete it in parts, thus avoiding the possible discomfort that a long questionnaire may generate in them. The pre-questionnaire part of each session will be completed at the beginning of the corresponding session and the post-questionnaire at the end of this session. They will have to complete a third questionnaire one month after the intervention in order to assess the maintenance of the acquired knowledge and behaviour. 

The pre- and post-intervention questionnaires will be completed with the help of 2–3 members of the research group, in addition to the school responsible teacher. They will help them to understand the questions they have to answer, always avoiding any influence. One month after the intervention, the post-questionnaire will be completed again with the help of the schoolteachers.

The control group will consist of a similar number of students to the intervention group; they will be part of the same school and their socio-demographic characteristics will be similar, even if they will be in the final year of the cycle. They will continue with the normal school curriculum. Students in the control group will be asked to complete a questionnaire as the intervention group, and they will have to answer it in the same month in which the intervention of the other group is being carried out. They will be helped by their teachers to understand the questions if necessary and will have to complete it in one session, since the aim is to avoid altering the usual routine of their classes.

Upon completion of the intervention, parents or guardians will be requested to fill out an online questionnaire to gather their feedback on the project as well as their children’s opinions, as reported by the parents.

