### 2.6. Outcome Measures

#### 2.6.1. Primary Outcomes

Due to the fact that the present intervention is based on competencies and learning outcomes, the results are also proposed according to them, differentiating between knowledge-related results and those related to behaviour, which are more difficult to achieve. The primary outcomes are shown in Table 3. 

As mentioned, the primary outcomes will be measured by a pre- and a postquestionnaire reported by children at the beginning of the session, before the activities and discussion of the topic, and at the end of the session. They will be measured again one month after the intervention.

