### 2.8. Statistical Analysis

The description of the characteristics of the participants and data from the pre-, post- and retention test (one month after) questionnaires will be reported per group (control and intervention). 

For the analysis of the differences between groups, a variety of statistical tests will be used depending on the type of response to the questions (continuous, discrete or qualitative). Based on the distribution of the variables of interest in the sample, descriptive statistics for continuous data will be presented using the mean and standard deviation or the median and interquartile range. Qualitative data shall be presented as frequencies and percentages. Quantitative variables will be analysed using an ANOVA of repeated measures test using the group as a factor of the independent level (parametric) or Wilcoxon’s test segmenting by group (non-parametric). On the other hand, qualitative variables in two categories will be analysed with Chi-square and Cochran’s Q tests. Finally, qualitative variables in more than two categories will be analysed with Chi-square and McNemar Bowker’s tests.

Data will be entered and analysed using SPSS 28.0 software. A confidence interval of 95% and significance level of *p* < 0.05 will be assumed.

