## Appendix A

**Table A1 nutrients-16-00338-t0A1:** Questionnaire to be completed by children to evaluate the intervention.

Competence	Question		Response
1	Do you know which foods are found in the different parts of the food pyramid?		Yes/No/No response
	Which foods are at the top of the pyramid?		Open question
	Which foods are at the bottom of the pyramid?		Open question
	Of the food pairs below, which do you think is highest in the food pyramid?		Tomato/Sweet, Pizza/Rice, Bread/Juice, Olive oil/Red meat, Potato/Ham
2	Of the foods you eat during the day, do you know which are unhealthy?		Yes/No
	Which are the unhealthy foods you eat?		Open question
	Are the foods that are often featured in advertisements usually healthy?		Yes/No/There is a bit of everything
	How much fruit and vegetables should you eat per day?		Open question
	What do you think you should improve your diet, for example, by eating more fruit, less sweets?		Open question
3	How many days a week do you usually take a healthy lunch to school (fruit, dairy products, wholemeal bread…)?		Scale 0 days–5 days
	Of the foods at the top of the food pyramid, how many do you eat at the weekend?		I eat them on Fridays, Saturdays and Sundays, more than once a day. I eat them on Fridays, Saturdays and Sundays, once a day. I only eat them one day at the weekend. I don’t eat them every weekend, only once in a while.
	Do you think it is important to eat a healthy diet?		No, if you do sport it is enough Yes, it is important but it is better for everyone to eat what they want Yes, it is very important for me.
	With what you have learned in these sessions, do you think you are able to improve your diet?		Yes, I know what mistakes I make in my diet and I am able to improve it Yes, I have learned a lot but I am not able to improve my diet No, I have not learned enough
	In the last month, have you eaten more, less or the same amount of the following food groups? (dairy products, fruits, vegetables, meat, fish, pulses, cereals, sweets)		Less/Equal/More/I do not know/No response
4	How much do you know about CD?		Scale 0 (nothing)–4 (much)
	What symptoms do people with CD have?		Open question
	When do people with CD develop symptoms?		Open question
	What compound in food is harmful to people with CD?		Open question
5	How do you think people with CD feel?		Open question
	Does a person with CD enjoy eating?		Scale 0 (nothing)–4 (much)

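### The competence 3 food-group item asks for change with no stated comparator and is repeated at one month, so its follow-up answers cannot separate a kept improvement from no change

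*Protocol article*

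**What the plan says.** **The item.** Appendix A, Table A1, competence 3 asks: "In the last month, have you eaten more, less or the same amount of the following food groups". It lists eight food groups: dairy products, fruits, vegetables, meat, fish, pulses, cereals and sweets. The answer options are "Less/Equal/More/I do not know/No response". No comparison period is named.

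**Its re-use.** Section 2.5.2 states: "One month after the intervention, the post-questionnaire will be completed again with the help of the schoolteachers". The purpose of the third questionnaire is given as "in order to assess the maintenance of the acquired knowledge and behaviour". Section 2.6.1 says of the primary outcomes: "They will be measured again one month after the intervention". The Discussion treats sustained knowledge and behaviour as essential to judging the programme.

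**The outcome served.** Table 3 links competence 3 to a primary outcome, change in the consumption of unhealthy foods.

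**The analysis.** Under section 2.8, "qualitative variables in more than two categories will be analysed with Chi-square" and McNemar-Bowker tests. No scoring rule is printed for this item, and neither is a reworded follow-up version.

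**The concern.** The answer is a change, not a level. The recall window is one month, the programme lasts four weeks (section 2.5.1), and follow-up comes one month after it. At follow-up, the period asked about is therefore the month after the programme. The most natural comparator is the programme month, when an improving child had already improved.

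Comparing such answers across waves or between groups treats them as repeated readings of one quantity, which they are not. What is at stake is the retention result on this item: the distribution of answers at one month can suggest that an effect has vanished when it has been fully kept.

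**Working it through.** No figure in the article is at issue, so there is none to reproduce. The check has three steps.

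**1. Truthful answers under each comparator.** Take a food the programme encourages, such as fruit, and assume the post answer is given near the end of the programme. At post, the child compares the programme month with the time before it. At one month, two readings are open: against the programme month (A) or against the time before the programme (B).

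| True course | Post | One month, A | One month, B |
|---|---|---|---|
| Improved and kept it | More | Equal | More |
| Improved, slipped partway | More | Less | More |
| Improved, slipped fully back | More | Less | Equal |
| Never changed | Equal | Equal | Equal |
| Improved only after the programme | Equal | More | More |

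For sweets, *Less* is the improving answer, so *More* and *Less* change places.

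- Under A, a child who kept the improvement and one who never changed give the same one-month answer. A between-group Chi-square at one month sees no difference between an intervention group that fully maintained and a control group that never changed.
- The sequence *More* then *Equal* means full maintenance under A and full relapse under B. The item does not tell the analyst which applies.

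**2. What the paired test registers.** The McNemar-Bowker statistic sums (n_ij − n_ji)² / (n_ij + n_ji) over pairs of categories. Assumptions: 60 intervention children, a share of whom improve and keep it fully, with all others answering *Equal* twice.

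Under A, the only off-diagonal cell is *More* to *Equal*, with count b. The statistic is (b − 0)² / (b + 0) = b.

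| Improvers | b | p, 1 df | p, 3 df |
|---|---|---|---|
| 10% | 6 | 0.014 | 0.11 |
| 20% | 12 | 0.0005 | 0.007 |
| 30% | 18 | 0.00002 | 0.0004 |
| 50% | 30 | <0.00001 | <0.00001 |

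One degree of freedom counts only the pair with observations. Three counts every pair among *Less*, *Equal* and *More*, with the other two options left out.

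Under B, the same children answer *More* twice, no cell is off-diagonal, and nothing is registered. If half the improvers use each comparator, then at 20% improvers b = 12 × 0.5 = 6, with p = 0.014 or 0.11. In all of these cases true retention is 100%.

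**3. Timing of the post answer.** Section 2.5.2 has each post part completed at the end of the corresponding session. Table 1 ties competence 3 both to Day 2 and to Days 2 to 8, and Table 2 places Day 2 in week 1. If the item is answered at the end of session 2, the month it covers lies mostly before the programme, and the *More* answers assumed above need not arise. The figures in step 2 would then not apply. The item still could not show maintenance, because its post answer would not describe the programme period.

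**The case against.** Five points can be made for the plan.

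- **No rule equates *Equal* at follow-up with loss.** This stands. A reader might infer that maintained improvement is counted as lost or tested as a reversal, but section 2.8 prints no scoring rule and does not name post versus follow-up as the contrast for this item. Bowker's test is one of symmetry; it registers a shift without labelling it.
- **The paired sequence carries more information than the one-month answer.** This stands in part. Under reading A, *More* then *Equal* differs from *Equal* then *Equal*, and also from *More* then *Less*. That helps only if all children use the same comparator, which the wording does not secure.
- **Children may compare with the time before the programme.** Some may, so a move from *More* to *Equal* is a possible result and not a certain one. The same true course then yields different answers from different children, which is the missing anchor again.
- **The primary behavioural outcome does not rest on this item.** This stands. Eight of the ten intake responses under competence 3 are of the change type (1 + 1 + 8 = 10), and a reader might conclude that maintenance of behaviour cannot be assessed. That goes too far. The school-lunch question (0 to 5 days) and the weekend question on foods at the top of the pyramid both ask for levels. Of the eight food groups, only sweets plainly represents unhealthy food.
- **Scoring can be left to an analysis plan.** This is true of scoring, but the wording is printed and its re-use is stated. No later analysis can recover the comparator each child had in mind.

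**Conclusion.** The point holds for this one item. Its wording does not fix what the child compares with, so the one-month answers cannot separate maintained improvement from no change. A paired comparison of post with follow-up can show full maintenance as a move away from *More* (or from *Less* for sweets).

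The size depends on the comparator children use. With 60 children, all improvers maintaining, and 10% to 50% improvers, the Bowker statistic runs from 6 to 30 if all compare with the programme month, and is 0 if all compare with the time before it. These figures are illustrative. They rest on the assumed group size and response pattern, and on a post answer given near the end of the programme, which section 2.5.2 does not guarantee.

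The documents do not support saying that the trial will score maintenance as loss, or that the maintenance objective fails for behaviour as a whole. The rewording is worth making before the first wave, because the ambiguity cannot be removed once the answers are in.

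**What to change.** Either of two changes is enough.

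1. **Anchor the comparison.** At post and at one month, ask whether the child now eats more, less or the same of each food group *compared with before [start month]*, using a fixed date before Day 1 and the same date for controls. Do not use the item as a pre-test question. Table A1 does not assign items to waves, so state this explicitly. The cost is one reworded line.
2. **Ask a level.** Ask current frequency over a fixed recent period for each food group, at every wave and in both arms, and analyse change in that level. The cost is a slightly longer answer for children and a possible ceiling for food groups eaten daily.

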## 2. Materials and Methods

### 2.1. Description

The Zeliakide project (the name comes from the union of two Basque words: “zeliako”, which means “celiac”, and “kide”, which means “companion”) is a one-month (4 weeks) intervention program, two-armed cluster, non-randomised and controlled trial, conducted among 10–12-year-old children with a pre- and post-intervention evaluation and 1 month follow-up to assess the effectiveness of the program.

The trial consists of a nutrition education intervention, focused on CD and the GFD. It is an intervention based on competencies and their respective learning outcomes. The teaching methodology chosen is inquiry-based learning (IBL). IBL enables children to acquire skills and knowledge through inquiry. It is a STEAM methodology that seeks to get children to ask questions, inspect, make measurements, design experiments, make logical reasoning based on evidence, and communicate the results.

The intervention is carried out by research experts in nutrition and CD, from the GLUTEN3S research team, and with experience in nutritional education activities. In addition, in order to highlight the role of women in science, they will be mainly women from this group who will go to the classroom to develop the intervention.

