	What would you do if it was your birthday and a classmate had CD?		Bring the cake that I like the most. Bring the cake that I like the most and another gluten-free cake for the person with CD. Bring a gluten-free cake for everyone. No response.
6	Where is the gluten?		Open question
	What makes a dough elastic?		Gluten Water I do not know
	How can we know (without experimenting) whether a food contains gluten or not?		Open question
	Which symbols indicate that a food does not contain gluten?		Open question
7	Which of the following foods a person with CD cannot eat?		Meat and fish Eggs and dairy Fruit and vegetables Wheat-based products: biscuits, bread and pasta Rice and maize Sweets They can eat anything I do not know
	From the following list of foods, which ones may contain gluten?		Raw rice, raw beans, fresh fruits, fresh vegetables, natural dairy products, fresh meat or fish, biscuits, some sweets, sweetened cocoa powder, some ice-creams, chocolate
	Can a prepared food (cream of vegetables, prepared beans…) have gluten, even if it is made from gluten-free ingredients?		Yes/No
8	Please rate these sentences according to your level of agreement.	In order to detect gluten, laboratory experiments must be carried out.	Scale 1 (not agree)–5 (very agree)
		It is important for scientists to do experiments.	Scale 1 (not agree)–5 (very agree)
		In the future I would like to become a scientist.	Scale 1 (not agree)–5 (very agree)
		Researchers are crazy, weird and male.	Scale 1 (not agree)–5 (very agree)

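### Twelve of the 32 questionnaire items are free text and feed primary outcomes; if the teaching team codes them from the original forms, coding could favour the programme, and masked coding is a cheap safeguard

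*Protocol article*

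**What the plan says.** Section 2.6.1 states that "the primary outcomes will be measured by a pre- and a postquestionnaire reported by children", with a repeat one month after the intervention. The instrument is Table A1 in Appendix A ("Questionnaire to be completed by children to evaluate the intervention"). Several of its items ask for a written answer in the child's own words, among them "What compound in food is harmful to people with CD" and "Which symbols indicate that a food does not contain gluten".

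On who is involved, section 2.1 says: "The intervention is carried out by research experts in nutrition and CD, from the GLUTEN3S research team". Section 2.5.2 says: "The pre- and post-intervention questionnaires will be completed with the help of 2–3 members of the research group", together with the responsible teacher, and adds the instruction "always avoiding any influence". The same section gives the one-month questionnaire to the schoolteachers to support, and has the controls helped by their own teachers where needed.

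On how the forms are filled in, section 2.5.2 has intervention children answer in parts, before and after each session, while controls answer in a single sitting.

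On what happens to the answers afterwards, section 2.8 says "Data will be entered and analysed using SPSS 28.0 software" and assigns tests by type of response. No coder, answer key or masking is named for the free text. The only scorer named anywhere is the research team, and only for the snack challenge (section 2.5.1), where a 1 / 0.5 / 0 key is given.

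**The concern.** A free-text answer has to be turned into a score or a category before any test in section 2.8 can use it, and that takes judgement. Whoever makes the judgement may give more credit to wording that echoes the lesson if they can see that an answer came after it, or from the intervention arm. That would add a difference in the programme's favour. A larger sample would not reduce it, and a comparison of groups or waves could not tell it from learning.

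The children, their teachers and the teaching team cannot be masked to the intervention. The coding of written answers can be, which makes this part of the bias avoidable. The limitations paragraph in the Discussion covers non-randomisation and the older control group, but not assessment.

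**Working it through.** **1. Count of Table A1.** The table gives no total, so there is no stated figure to reproduce. Each row is counted as one item, and each of the four competence 8 statements as one.

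| Competence | Open | All |
|---|---|---|
| 1 Food pyramid | 2 | 4 |
| 2 Dietary errors | 3 | 5 |
| 3 Eating less unhealthy food | 0 | 5 |
| 4 Celiac disease | 3 | 4 |
| 5 Impact of own actions on others | 1 | 3 |
| 6 Gluten | 3 | 4 |
| 7 Foods by gluten content | 0 | 3 |
| 8 Science | 0 | 4 |
| Total | 12 | 32 |

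12/32 = 37.5%. Table 3 ties competences 1, 2, 4, 6 and 7 to knowledge outcomes. Their open items are 2 + 3 + 3 + 3 + 0 = 11, out of 4 + 5 + 4 + 4 + 3 = 20, or 55%. In competence 4 the only closed item is the child's 0–4 rating of their own knowledge, so every item there that tests knowledge is free text.

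**2. Who touches the answers.**

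| | Intervention, pre and post | Intervention, one month | Control |
|---|---|---|---|
| Help from | 2–3 research members plus teacher | schoolteachers | teachers |
| Format | parts, by session | not described as in parts | one sitting |
| Coder of free text | not named | not named | not named |

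The teaching team's presence therefore covers the intervention pre and post waves only. The difference in format means that an original form may show its arm and, in the intervention arm, whether it was filled in before or after the session. Form layout is not described, so this is a possibility and not a stated fact.

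**3. How much leniency would matter (illustration).** The assumptions are mine: m items scored 0/1, each correct with probability 0.5 (variance 0.25), and a common inter-item correlation r from 0 to 0.3. Extra credit on all 11 open knowledge items, in one arm or wave only, shifts the mean by 11 × δ. Setting that equal to the planning effect in section 2.3 (Cohen's d = 0.32):

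SD = √(m × 0.25 × (1 + (m − 1) × r)), and δ = 0.32 × SD / 11.

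| Score | r | SD | δ, percentage points |
|---|---|---|---|
| 11 open items | 0 | 1.66 | 4.8 |
| 11 open items | 0.1 | 2.35 | 6.8 |
| 11 open items | 0.2 | 2.87 | 8.4 |
| 11 open items | 0.3 | 3.32 | 9.6 |
| 20 knowledge items | 0 | 2.24 | 6.5 |
| 20 knowledge items | 0.1 | 3.81 | 11.1 |
| 20 knowledge items | 0.2 | 4.90 | 14.3 |
| 20 knowledge items | 0.3 | 5.79 | 16.8 |

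Two open items in competence 2 (unhealthy foods the child eats, and what to improve) have no single correct answer. If leniency can act on only 9 items of the 20-item score, δ rises to 0.32 × 2.24 / 9 = 8.0 points at r = 0 and 0.32 × 5.79 / 9 = 20.6 points at r = 0.3.

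The table shows how sensitive such scores are. It does not estimate any bias that will occur.

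**The case against.** The strongest reply is that the article is silent here. It condenses a fuller protocol, and a coding manual, an answer key and coder masking are commonly left to that document. This stands. A reader might infer that the open answers will be coded unmasked by the people who taught the lessons; the article does not say so. Helping children to answer does not show who codes, and the snack scoring is a different task. What remains is a conditional risk built from stated choices: free text in primary outcomes, a teaching team present at two intervention waves, and formats that differ by arm.

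The article also holds points that narrow the risk. Helpers are told not to influence answers, although that instruction concerns helping and not coding. Schoolteachers support the one-month questionnaire, so the team's presence does not reach that wave, though the coding question does. Not all 12 items can be marked right or wrong, and some that can leave little room for judgement: the question on the harmful compound has essentially one answer.

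Two further readings are tempting and unsupported. One is that these are the outcomes on which the trial chiefly rests. Table 3 does not rank its outcomes, section 2.3 raises the sample from 60 to 120 for attitude, and the Discussion describes the target as about one point on a 0–4 scale, while the only items in Table A1 on such a scale are closed. The other is to take a single item, say 60% against 50% credited (Cohen's h = 0.20), and report it as a share of the planned 0.32. That sets an effect on one binary item against a standardised difference on an undefined score.

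**Conclusion.** The concern holds in conditional form. The count is exact: 12 of 32 items are free text, including 11 of 20 knowledge items and all the celiac-disease items except a self-rating, and they feed primary outcomes. If the research team codes them from the original forms, coding could favour the programme, and the analysis in section 2.8 could not detect it.

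The size of any such bias is unknown. Under 0/1 scoring with p = 0.5 and r between 0 and 0.3, differential credit of about 5 to 10 points per open item on an 11-item open score, or about 7 to 17 points on a 20-item knowledge score, would match d = 0.32. If fewer items are open to judgement on the 20-item score, more leniency per item is needed.

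This is a worthwhile, inexpensive improvement to how primary outcome data are produced. It is not evidence that the planned coding is biased.

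**What to change.** - Before any coding starts, write an answer key for the open items that have a correct answer, and a category scheme for those that do not (for example the unhealthy foods the child eats, and how people with CD feel).
- Transcribe all open answers verbatim. Pool both arms and all waves in random order, with arm, wave, school and form type removed.
- Have an existing team member code the pooled list against the key and scheme.
- Lock the scores, and only then merge arm and wave back in.
- State this in the protocol. If the full protocol already describes an equivalent procedure, a sentence pointing to it is enough.

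The cost is a few days of transcription and a written key, with no new staff and no change to the intervention, questionnaire or sample. Each transcribed answer needs a study code for the merge; the repeated-measures analysis already requires linking a child's waves. Masking will be partial, because wording taken from the lessons may hint at arm or wave. Fixing the key beforehand limits what a coder can do with that hint.
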